For the *trained skills assessment*, study staff will code how dispatchers perform on each of eight training points using a detailed codebook developed to match each call’s script, training points and feedback. This codebook was tested with ten call audio recordings and refined in collaboration with the simulation training instructor. Staff engaged in three hours of training to familiarize themselves with the coding scheme and the codebook instructions. Then staff coded and conducted the trained skills assessment on eight calls. Coding and trained skills assessment results were identical (Kappa statistic = 1). The codebook defines how study staff is to complete the trained skills assessment form: Table 3.

**Table 3 Tab3:** Trained Skills Assessment

Training Point Measurement	Result (yes/no/NA)
Does not get distracted by label at any point in the call	
Asks consciousness according to protocol script (Conscious/awake)	
Follows-up on first consciousness answer appropriately	
Closes consciousness inquiry after at most two unclear answers	
Asks breathing according to protocol script (breathing normally)	
Follows-up on first breathing answer appropriately	
Closes the breathing inquiry after at most two “not normal” breathing answers	
Transitions to appropriate pre-arrival instructions (T-CPR) promptly	

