#### Power calculations

Initial sample size calculations called for 180 dispatchers. After collecting preliminary data, sample size calculations were repeated using updated parameter estimates of a baseline recognition rate of 70 %, a 20 percentage point improvement in recognition rate, a baseline median time to start T-CPR of 75 s, a 30 % reduction in the mean time to start T-CPR, and a conservative within individual correlation of 0.5 for both rate of recognition and time to start of CPR instructions. Under these assumptions we calculate we will need data on 140 dispatchers to have 80 % power of rejecting the null hypothesis of no change in the rate of recognition and 80 % power of rejecting the null hypothesis of no change in the time to start T-CPR, at the alpha = 0.05 level each. Power for the rate of recognition was calculated using the two-sample *t*-test given in the statistical analysis section of Lenth [23]. Power for time to start of T-CPR was calculated for simulation using the accelerated failure time analysis described in the statistical analysis section, but without adjustment for actor variation or script differences.

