## Statistical analysis

### Primary aim analyses: differences in performance during the simulation test

The primary aim analyses will compare the rate of recognition of the need for T-CPR and the time to the start of T-CPR instructions between the intervention and control arms during the simulation test. The rate of recognition of the need for T-CPR will be compared between the intervention and control arms using a two sample *t*-test on the proportion of two T-CPR appropriate assessment calls for each individual (0, ½ or 1; each dispatcher completes two test calls).

The time to start of T-CPR is a potentially right-censored measurement; if the call receiver does not recognize the need for T-CPR prior to the end of the call, then the time until starting T-CPR is only known to be *at least* as long as the call duration (In practice, recognition of the need for CPR will occur in all cases when paramedics arrive on scene and attend to the patient). As the time to start of T-CPR must be analyzed using methods that can deal with censored observations, we will use an accelerated failure time model with log-logistic distribution to test the effect of randomization group. Standardized caller and call scenario will be included as covariates to allow for differences in standardized caller speaking speed and the complexity of the scripts, and allowing for a within subject correlation by using robust estimates of standard error.

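### Test calls without T-CPR are censored at their own length, so the primary time ratio partly reflects failed-call length if that length differs between arms

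*Protocol article*

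**What the plan says.** The Protocol article (Statistical analysis, Primary aim analyses) treats time to T-CPR as right-censored. The rule is that "if the call receiver does not recognize the need for T-CPR prior to the end of the call, then the time until starting T-CPR" has a lower bound and no observed value: it "is only known to be *at least* as long as the call duration". The model is then named: "we will use an accelerated failure time model with log-logistic distribution to test the effect of randomization group". Standardized caller and scenario are covariates, and the two calls per dispatcher are handled by "allowing for a within subject correlation by using robust estimates of standard error".

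The only reason given for a start time beyond the call end is that "In practice, recognition of the need for CPR will occur in all cases when paramedics arrive on scene and attend to the patient". That describes real emergencies. The sections on the intervention and procedures describe no paramedic arrival in a mock call. They give no fixed or maximum length for a mock call, and they do not say whether the dispatcher, the caller's script or the instructor ends one in which T-CPR has not started.

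Table 1 measures recognition, the other primary outcome, by whether T-CPR instructions start. Power calculations assume "a baseline recognition rate of 70" per cent and a gain of 20 percentage points.

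**The concern.** A call is censored exactly when the dispatcher fails the other primary outcome. The AFT model nevertheless treats it as a call that would have reached T-CPR later, with the same prospects as any other call still running at that moment. A call that fails early is therefore penalized less than one that fails late, although neither led to T-CPR.

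On the plan's own figures about 30% of control calls (1 − 0.70) and 10% of intervention calls (1 − 0.90) would be censored, so the rule affects a sizeable share of the data. If training changes how long failed calls last, the time ratio can move when neither recognition nor start times have changed. It can create a benefit or hide one.

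**Working it through.** **1. The plan's own figure.** For recognition, the variance of a dispatcher's mean over two calls is p(1−p)(1+ρ)/2. With ρ = 0.5 this is 0.1575 at p = 0.70 and 0.0675 at p = 0.90. A two-sample t-test for a 0.20 difference then needs 92 dispatchers (unequal variances) to 126 (baseline variance in both arms), and 140 give 94% or 84% power. For time, with a 75 s median, time ratio 0.70 and ρ = 0.5, 140 dispatchers give about 80% power if the log-logistic shape is about 2 (80% uncensored, 82% with 30% of control calls censored). Shape 1.5 gives 54–60% and shape 3 about 99%. The article does not state the shape, so 140 is compatible but cannot be confirmed. Nothing below depends on it.

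**2. What the model infers for a failed call.** With S(t) = 1/(1 + (t/75)^k), a call censored at c has a model-based median start time m that solves S(m) = S(c)/2, so m = 75 × [1 + 2(c/75)^k]^(1/k).
- c = 60 s: k = 2 gives 75 × √2.28 ≈ 113 s; k = 3 gives 75 × 2.024^(1/3) ≈ 95 s.
- c = 180 s: k = 2 gives 75 × √12.52 ≈ 265 s; k = 3 gives 75 × 28.648^(1/3) ≈ 230 s.

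Two equal failures thus count as very different times because of call length alone.

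**3. Simulation with no training effect on T-CPR.** From the article: 70 dispatchers per arm, two calls each, correlation 0.5, 75 s median, 70% recognition (here in both arms). Assumed: shape 3, failed-call lengths as listed with log-SD 0.3, two-sided 5% test, common horizon 300 s. The model is a log-logistic AFT with dispatcher-clustered standard errors, without caller and scenario covariates. Own-length results use 1,500 replicates and common-horizon results 500.

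| Failed-call length, control / intervention | Own length: time ratio | False benefit | Common 300 s: time ratio | False benefit |
|---|---|---|---|---|
| 180 / 180 s | 1.01 | 1.9% | 0.99 | 3.0% |
| 180 / 150 s | 0.96 | 4.0% | 1.00 | 2.0% |
| 180 / 120 s | 0.92 | 8.7% | 1.01 | 3.4% |
| 180 / 90 s | 0.87 | 21% | 1.00 | 2.0% |
| 240 / 120 s | 0.88 | 15% | 0.99 | 1.8% |
| 120 / 180 s | 1.08 | 0.2% (false harm 8.2%) | 1.01 | 2.8% |

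Nominal false benefit is 2.5%. Total error under the common horizon was about 4–6%. Repeat simulations put 180 / 120 s at about 9–11%, and 180 / 90 s at 17–26% with ratios of 0.86–0.88. Shapes 2 and 5 give 0.92 and 0.93 for 180 / 120 s.

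**4. Direction can reverse.** With worse recognition under training (65% against 70%) and failed calls of 90 s under training against 180 s in control, the own-length rule still favors training: ratio 0.91, significant benefit in 11%. A common 300 s horizon gives 1.14.

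**5. Where it does little or no harm.** At 90% recognition in both arms, 180 / 90 s gives 0.965 and 5% false benefit. If the call end really is independent of the start time, unequal lengths leave the ratio at 1.00 and total error at 5%.

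**The case against.** The strongest reply is that the decisive fact is missing. A reader might infer that the dispatcher ends a failed call by misjudging it and wrapping up, but the article refers only to call duration. Callers are scripted and an instructor listens in. If the script or the instructor ends every such call at one common time, the between-arm problem disappears. This stands, and it makes the point conditional.

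A reader might also infer from Table 3 that training shortens failed calls, because dispatchers are scored on "Closes consciousness inquiry after at most two unclear answers". The documents do not support that. Closing an inquiry there means moving on, and the list ends with a prompt transition to T-CPR. It shows that inquiry length is a training target; it does not show in which direction failed-call length would change.

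Nor is a lower time ratio a false benefit when recognition truly rises from 70% to 90%. With identical start times among recognizers, the ratio runs from 0.92 when failed calls in both arms end at 60 s, through 0.76 at 180 s, to 0.65 at 420 s. The direction is right for an outcome that counts missed calls as late. The series shows that the size depends on the length used, and this limits a common-horizon AFT analysis as well.

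How a mock call ends may be described in the full protocol or SAP. The censoring rule and the model, however, are stated in the article for a primary outcome, so they can be judged as written.

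**Conclusion.** The point holds in conditional form. Censoring each failed test call at its own length makes the primary time ratio depend partly on failed-call length, and the article fixes nothing that keeps this length equal between arms. Under no effect on recognition or start times, a one-third shorter failed call in the intervention arm (120 against 180 s) gives a ratio of about 0.92 and a false benefit in about 9–11% of trials. Halving it gives about 0.87 and 17–26%.

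This rests on assumed failed-call lengths, an assumed log-logistic shape, 70% recognition, and call ends that reflect failure and not independent censoring. The distortion is modest when lengths differ by less than about a third or few calls fail. It would be wrong to conclude that type I error is inflated regardless: with equal lengths total error was 4.2%. Recognition is tested separately and is not affected.

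The conclusion concerns the simulation test only. A reader might carry it over to actual calls (secondary aim 2), but those have no scripted maximum, and the arrival of emergency services can genuinely end follow-up at varying times.

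**What to change.** For the simulation test, state how a mock call without T-CPR ends. Prespecify one horizon for both arms, for example the scripted maximum mock-call length, and set every call without T-CPR to it whatever its actual length. Then either fit the planned AFT model to these times, or analyze restricted mean time to T-CPR up to the horizon with dispatcher-clustered standard errors. Show one alternative horizon, and report time among calls with T-CPR descriptively. Do not extend the fixed horizon to actual calls without a separate justification.

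This changes analysis wording only and needs no new data; it should be settled before unblinded analysis. The downside is that the size of the estimate depends on the chosen horizon and partly restates the recognition difference. With a 420 s horizon, 70% against 90% recognition and identical start times averaging roughly 91 s among recognizers, the restricted-mean difference is about 0.20 × (420 − 91) ≈ 66 s in favor of training, all of it from recognition. The descriptive report of times among calls with T-CPR is there to make that visible.

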### Secondary aims 1 & 2 analyses: effect of the intervention on actual cardiac arrest 9-1-1 calls

Dispatchers will have varying numbers of observations depending on how many actual cardiac arrest calls they receive during their study period. The recognition of the need for T-CPR will be analyzed using a random slopes mixed-effects logistic regression model, with 9-1-1 call center included as a covariate, and dispatcher as the random effect. The time to start of T-CPR will be analyzed using a parametric regression frailty model, with 9-1-1 call center included as a covariate, and dispatcher as the random effect.

### Secondary aim 3 analysis: differences in call processing skills during the simulation test

We will compare performance on the eight skill measures on the trained skills assessment between the intervention and control arms during the simulation test. The binary results for each of the eight skill measures (Table 3) will be compared across experiment arm (intervention v. control) using two-sample t-tests comparing the proportion of each skill (out of the two assessment calls) correctly demonstrated, if tested. Using the proportion as the outcome allows the denominator to vary between dispatcher, as not every skill is tested in every call. For example, if a dispatcher never conducts a consciousness inquiry, but first asks about breathing and then immediately starts T-CPR, then performance on the “follows-up on first consciousness answer appropriately” skill is not tested.

### Secondary aim 4 analysis: effect of the intervention on self-confidence

The effect of the intervention on change in self-confidence will be analyzed using a multivariate linear regression model with group and baseline self-confidence score as covariates and self-confidence score as reported on the follow-up survey as the outcome variable.

### Secondary aim 5 analysis: cost and cost-effectiveness

A cost of the intervention as implemented will be described with a focus on three types of costs: the design, the time of the instructor, and the time of the standardized patients and dispatchers. Data on the design costs are available from project financial records and can be spread across the trial participants and future participants if the intervention is adopted widely. The instructor is tracking his time on a random sample of days to estimate the ratio of time devoted to scheduling call sessions relative to time conducting, listening, and providing feedback during the call sessions. The time of the instructor, standardized patients and dispatchers is tracked during every training session and valued at average salaries for each profession. The cost analysis will also include projections of cost of the intervention when the trainings are conducted by supervisors at the call centers rather than the instructor on the project team.

An optional cost-effectiveness analysis may be conducted to estimate the cost per cardiac arrest patient who survives to hospital admission. We are working with the Public Health: Seattle & King County (PHSKC) Cardiac Arrest Surveillance System (CASS) with data on all cardiac arrest cases from 2001 to 2010 (*n* = 6357) to estimate parameters of a cost-effectiveness model. We plan to estimate the effect of bystander CPR on survival and costs of hospitalization. Preliminary estimates suggest that bystander CPR (T-CPR and unassisted) affects survival until hospital admission, but not other outcomes after hospitalization. If the same is true for hospital costs, we would focus on the cost per patient who survives to hospital admission, because survival and costs after hospital admission would be the same as other cardiac arrest patients.

## Discussion

Absent medical attention, chances for cardiac arrest survival decrease sharply with every minute after breathing stops. 9-1-1 dispatchers are often the first contact with a health care system for bystanders to cardiac arrest, and can improve health outcomes by quickly identifying suspected cases of cardiac arrest and promptly starting T-CPR. Previous research indicates that experience handling such calls may improve dispatcher recognition of cardiac arrest, but no studies have looked at a way to increase this experience through simulation. The STAT-911 study will evaluate the potential for using phone-based simulation training to increase dispatcher experience with cardiac arrest calls and improve their processing of medical emergency calls. It will also advance knowledge regarding best-practices in use of phone-based simulations for any health professionals who need to make treatment and triage decisions during phone-interactions with clients, patients, or bystanders. Although the use of “standardized patients” has been standard and effective in training health care providers in medical procedures and patient interaction, the use of “standardized callers” for training phone-operators in diagnosis, triage and treatment decisions is a novel application of this type of simulation training method and an exciting new area for research.
